### Data collection

2.9

During the screening period, the participants will complete a questionnaire regarding their sociodemographic characteristics, provide their medical history, undergo a physical examination in the lumbar region, and rate their pain using the VAS.

Personal information and data collected during the screening period will be shared and managed by the hospital. As the researchers are clinical, a data monitoring committee is not needed. The final trial dataset is accessible to statisticians and principal investigator.

The schedule for treatment and outcome measurements is presented in Table 2. Visits 1 to 6 will include the treatment sessions, while visit 7 will be the follow-up visit after treatment completion.

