#### Primary outcomes

2.10.1

The change in the VAS score for pain from baseline (visit 1, first treatment session) to the follow-up visit after treatment completion (visit 7) will be assessed as the primary outcome.

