#### Secondary outcomes

2.10.2

The following will be assessed as secondary outcomes: changes in the VAS score for pain from baseline (visit 1) to visits 3 (third session) and 5 (fifth session); changes in the VAS score for pain at all assessment points from baseline (visit 1) to the follow-up visit (visit 7); changes in the ODI from visit 1 to visits 3, 5, and 7; and the change in ODI at all assessment points from visit 1 to visit 7.

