### Sample size

2.13

The sample size will be calculated as per the results of previous trials on electroacupuncture therapy for chronic low back pain, because there are no available studies on electromagnetic acupuncture therapy. We assume that the effect of electromagnetic acupuncture would at least be equivalent to those of electroacupuncture; therefore, we will refer to the effect size of electroacupuncture therapy as conservative treatment for low back pain. In a previous study, the mean difference in the follow-up VAS score for pain was 0.87 between groups, with an estimated standard deviation of 1.48.^[17]^ The alpha level is 5% for both sides, and the study power is maintained at 80%. A total of 52 participants will thus be required in each group after considering an attrition rate of 10%.

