### Statistical analysis

2.14

Statistical analysis will be primarily based on the intent-to-treat principle, although per-protocol principles will also be checked. The missing values will be analyzed by the last observation carried forward method. The significance level will be set at *P* < .05, and the confidence interval at 95%. All statistical analyses will be performed using SPSS Statistics for Windows Version 20.0 (IBM Corp., Armonk, NY). There is no intermediate analysis of this study, and the final decision on end of trial is with principal investigator.

Differences in sociodemographic and baseline characteristics between the EMA and sham groups will be evaluated. For continuous data, Student *t* test or the Wilcoxon rank sum test will be performed. For categorical data, the Chi-square test or Fisher exact test will be used.

Changes in VAS and ODI scores from baseline to each assessment point will be assessed using Student *t* test or the Wilcoxon rank sum test, while those at all evaluation points from baseline to the follow-up visit will be assessed using repeated measures analysis of variance (RM-ANOVA). The incidence of adverse events will be investigated using the Chi-square test or Fisher exact test.

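### The primary outcome is tested on unadjusted change scores; an ANCOVA on the visit-1 value already collected would generally be more precise at no cost in data.

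*Protocol article*

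**What the plan says.** Section 2.10.1 of the protocol article defines the primary outcome: "The change in the VAS score for pain from baseline (visit 1, first treatment session) to the follow-up visit after treatment completion (visit 7". Section 2.10.2 adds VAS changes to visits 3 and 5 and, for disability, "changes in the ODI from visit 1 to visits 3, 5, and 7".

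Section 2.14 gives the analysis: "Changes in VAS and ODI scores from baseline to each assessment point will be assessed using Student". The sentence means the *t* test, and it offers a rank sum test as the alternative. The visit-wise comparisons, including the primary one, are therefore two-sample tests on change scores, with no covariate named. The repeated-measures analysis belongs to the separate all-time-points outcomes and names no covariate either.

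Section 2.13 sizes the trial on a quantity described as a follow-up score: "the mean difference in the follow-up VAS score for pain was 0.87 between groups, with an estimated standard deviation of 1.48". The design values are a two-sided 5% level, 80% power, 10% attrition and 52 per group.

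**The concern.** A change score subtracts the baseline value in full, so its regression coefficient is fixed at 1. ANCOVA estimates the coefficient from the data. When the true slope of follow-up on baseline is below 1, full subtraction overcorrects. It adds variance, and a chance difference between the groups at visit 1 moves the estimated effect in the opposite direction.

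The baseline value is on file for every patient who contributes a change score, so the lost precision could be recovered without new data. At stake are the power of the primary comparison in a trial of 104 patients, and how far its estimate depends on chance baseline differences. Section 2.5 describes blocks and mentions no stratification by pain. Section 2.14 compares baseline characteristics between groups but names no analysis that would adjust for a difference.

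**Working it through.** **Inputs from section 2.13.** Difference 0.87, SD 1.48, two-sided 5%, 80% power, 10% attrition, 52 per arm.

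**Assumed, because the article gives no value.** Correlation r between visit-1 and visit-7 VAS of 0.3, 0.5 and 0.7; and the baseline SD, on the same scale as 1.48.

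**1. The plan's own figure.** n = 2 × [(1.960 + 0.842) × 1.48 / 0.87]² = 45.4, so 46 per arm; 46 / 0.9 = 51.1, so 52. The stated number reproduces and the sample-size arithmetic is not at fault.

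**2. Formulas.** With baseline SD B and follow-up SD F:
- SD of change = √(B² + F² − 2rBF)
- ANCOVA residual SD = F√(1 − r²)
- slope of follow-up on baseline = rF/B

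With B = F, the variance ratio of change score to ANCOVA is 2/(1 + r): 1.54 at r=0.3, 1.33 at r=0.5 and 1.18 at r=0.7. In general the two variances are equal when the slope is 1.

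**3. SDs in each scenario (change / ANCOVA).**
- A. 1.48 is the follow-up SD, as section 2.13 words it, and B = 1.48: 1.751 / 1.412 at r=0.3, 1.480 / 1.282 at r=0.5, 1.146 / 1.057 at r=0.7.
- B. 1.48 is the follow-up SD and B = 1.0, a narrower baseline that is plausible given the 40 mm entry minimum: 1.517 / 1.412, 1.308 / 1.282, 1.058 / 1.057. The variance ratios fall to 1.16, 1.04 and 1.00. At r=0.7 the slope is 0.7 × 1.48 / 1.0 = 1.04, so the two analyses almost coincide.
- C. 1.48 is the SD of change and the SDs are equal: ANCOVA SD = 1.48√((1 + r)/2) = 1.193, 1.282 and 1.364.

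**4. Power for a difference of 0.87** (two-sample t, two-sided 5%; the one degree of freedom spent on the covariate is ignored). 47 is 52 × 0.9 = 46.8, rounded up; 46 is the number before attrition; 52 is everyone randomised, as under LOCF, with difference and SD held unchanged.

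| Scenario | n per arm | r=0.3: change vs ANCOVA | r=0.5 | r=0.7 |
|---|---|---|---|---|
| A | 47 | 66% vs 84% | 80% vs 90% | 95% vs 98% |
| A | 52 | 71% vs 88% | 84% vs 93% | 97% vs 99% |
| B | 47 | 79% vs 84% | 89% vs 90% | 98% vs 98% |
| C | 46 | 80% vs 93% | 80% vs 90% | 80% vs 86% |

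**5. Sensitivity to chance imbalance.** A baseline difference Δ moves the change-score estimate by (slope − 1) × Δ. In scenario A with 47 per arm, a one-standard-error imbalance is 1.48 × √(2/47) = 0.305. At r=0.5 the shift is 0.5 × 0.305 = 0.15 in size, about 18% of 0.87. It is zero when the slope is 1.

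**The case against.** The strongest reply is that the planned test is sound and the gain may be small. Both parts stand to a degree. Under randomisation the change-score comparison is unbiased on average, and the lack of stratification does not alter that. The largest gains need a low r together with equal SDs and 1.48 read as the follow-up SD. Scenario B shows the gain shrinking to 5 points or fewer, and to nothing at r=0.7. What this does not remove is that ANCOVA is, in large samples, never less precise.

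A second reply is that the article is a condensed account. That would excuse an omission, but here the article states the test for the primary outcome.

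Four stronger readings are tempting and are not supported:
- A reader might infer that the analysis ignores baseline. It does not; a change score uses it with coefficient 1.
- A reader might infer that the change score is always less precise unless r is 1. That holds only with equal SDs; the general exception is a slope of 1, which can occur at r below 1.
- A reader might infer from the two named tests that the primary test will be picked after seeing the data, with an inflated type I error. The article does not say so. A selection rule is a detail an article may leave to the full protocol or SAP, and nothing suggests that the smaller P value would be taken.
- A reader might infer that the statisticians who assign codes (section 2.5) also choose the test. Section 2.9 says only: "The final trial dataset is accessible to statisticians and principal investigator". Neither section says who chooses.

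**Conclusion.** The point holds as one of efficiency and of robustness to chance imbalance, not of validity. Section 2.14 fixes a primary test that is generally less precise than one using the same data.

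Across the values examined, the gain in power from ANCOVA runs from none (scenario B, r=0.7) to 18 points (scenario A, r=0.3, 47 per arm). In scenario A at 47 per arm, the planned test reaches 80% only from r of about 0.5 upwards, whereas ANCOVA is at 84% or more at all three correlations. In scenario C the planned test has its 80% and ANCOVA adds 6 to 13 points.

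All of this rests on assumed correlations and SD ratios, and on which SD the 1.48 is. The figures compare the t test with ANCOVA for VAS; the article gives no SD for ODI, so no size is claimed there. The change should be made, but the trial is not invalid without it.

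**What to change.** In section 2.14, name one primary analysis: an ANCOVA of visit-7 VAS on treatment group with visit-1 VAS as covariate, reporting the adjusted mean difference, its 95% confidence interval and the P value. Use the same model for VAS at visits 3 and 5 and for ODI at visits 3, 5 and 7, each with its own visit-1 value as covariate. Keep the Wilcoxon rank sum test as a labelled sensitivity analysis that cannot replace the primary result.

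The cost is a sentence or two of analysis wording. No extra data, visits or patients are needed, and the SPSS version already named can fit the model.

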## Discussion

3

Of late, nonpharmacological therapies for chronic low back pain have gained popularity as replacements for medication or surgery. In the field of oriental medicine, various treatments, such as acupuncture, electroacupuncture, pharmacopuncture, and acupotomy, are used for chronic low back pain.

Magnetic fields are used to treat various diseases.^[18]^ Use of electromagnetic stimulation therapy has been reported for inducing muscle relaxation,^[9]^ treating Bell palsy^[19]^ as well as musculoskeletal pain.^[20,21]^ To the best of our knowledge, this will be the first study on the use of electromagnetic acupuncture for the treatment of chronic low back pain.

This study design is expected to have some advantages. In order to verify the efficacy of electromagnetic acupuncture for chronic low back pain, the acupoints and procedure have been standardized. In addition, the placebo device will appear and sound, and be used, in the same way as the Whata153, ensuring a double-blind protocol. Moreover, RM-ANOVA will be used to assess not only the reduction in pain at a certain point in time but also differences in the amount of pain reduction over time.

The results of this trial will provide important clinical information about the efficacy and safety of electromagnetic acupuncture, which is expected to cause less discomfort and provide better results than electroacupuncture, for chronic low back pain. We believe that this treatment will relieve pain and improve the quality of life for many patients experiencing chronic low back pain. Because this is a pilot trial, we will analyze the data from various aspects and use statistical methods that will help in providing a foundation for the final clinical trial. If this study is successful, we expect that further studies on electromagnetic acupuncture for other clinical diseases will be designed and performed.

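### RM-ANOVA for the secondary all-visit VAS and ODI outcomes names no baseline covariate and leaves its response open to two readings; a baseline-adjusted mixed model would do better at no cost

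*Protocol article*

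**What the plan says.** The Secondary outcomes section lists, besides single-visit changes, "changes in the VAS score for pain at all assessment points from baseline (visit 1) to the follow-up visit (visit 7" and "the change in ODI at all assessment points from visit 1 to visit 7". The Statistical analysis section splits the methods in one sentence. It opens "Changes in VAS and ODI scores from baseline to each assessment point will be assessed using Student" (t test, or Wilcoxon rank sum test) and continues that "those at all evaluation points from baseline to the follow-up visit will be assessed using repeated measures analysis of variance (RM-ANOVA". The same section fills missing values by LOCF and names SPSS 20.0. Beyond the words "will be assessed using repeated measures analysis of variance (RM-ANOVA", it names no baseline covariate, no tested term and no treatment of non-sphericity.

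The Discussion presents RM-ANOVA as a strength of the design because it assesses "differences in the amount of pain reduction over time". The primary outcome is separate: "The change in the VAS score for pain from baseline (visit 1, first treatment session) to the follow-up visit after treatment completion (visit 7". It falls under the t test or Wilcoxon test.

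**The concern.** The analysis sentence can be read in two ways. Its grammar makes changes from baseline the response, which leaves three occasions (visits 3, 5 and 7). Its reference to all points from baseline to follow-up can also mean raw scores at four occasions, with visit 1 included. RM-ANOVA offers two between-arm tests, the arm main effect and the time-by-arm interaction, and which of them is informative depends on the layout:

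- With visit 1 as a response occasion, the arm main effect averages in a visit at which randomised arms differ only by chance.
- With changes as the response, the interaction asks only whether the arm difference varies between visits 3, 5 and 7. It does not ask whether there is a difference.

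The same data could therefore be reported as showing no difference over time or a clear one, depending on a choice made later. Neither layout uses baseline as a covariate, which costs precision. Classical RM-ANOVA also needs complete rows, which ties it to the LOCF rule. The layout problem remains even with no missing data.

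**Working it through.** **The plan's own figure.** Inputs from Sample size: difference 0.87, SD 1.48, two-sided 5%, power 80%, attrition 10%. n = 2(1.96 + 0.84)² × (1.48/0.87)² ≈ 45.4, so 46 per group. 46/0.9 = 51.1, so 52. The stated 52 per group is reproduced and does not depend on RM-ANOVA.

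**Assumptions.** The document gives no correlations between visits. The check assumes 52 complete patients per arm, SD 1.48 at each visit, and either compound symmetry (CS) 0.5 or AR(1) 0.5, 0.7 or 0.9. Three further scenarios let the SD rise from baseline. The visit-7 effect is 0.87/1.48 = 0.59 SD.

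**Dilution.** Take an effect growing linearly: 0, 0.29, 0.58, 0.87 at visits 1, 3, 5, 7.
- Mean over four occasions: 1.74/4 = 0.435.
- Mean over visits 3, 5, 7: 1.74/3 = 0.58.
- Ratio: 0.435/0.58 = 0.75.

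**Power of the arm effect, worked for CS 0.5 in SD units.** Power ≈ Φ(δ/SE − 1.96), with SE = √(2V/52).
- Raw scores, four occasions: δ = 0.435/1.48 = 0.294; V = (1 + 3×0.5)/4 = 0.625; SE = 0.155; ratio 1.90; power about 47%.
- Changes, three occasions: δ = 0.58/1.48 = 0.392; V = 0.667 + 1 − 2×0.5 = 0.667; SE = 0.160; ratio 2.45; power about 69%.
- Mean of visits 3, 5, 7 adjusted for baseline: δ = 0.392; V = 0.667 − 0.5² = 0.417; SE = 0.127; ratio 3.10; power about 87%.

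Simulation gives 47% and 68% for the first two. Across the assumed equal-SD covariances the ranges are about 36 to 55% (raw scores), 47 to 96% (changes) and 77 to 98% (baseline-adjusted average). With the rising-SD scenarios included, the raw-score arm effect has 36 to 62%.

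**Power of time-by-arm.** For the linear effect with Greenhouse-Geisser correction:

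| Covariance | Visit 1 in vector | Changes |
|---|---|---|
| CS 0.5 | 75% | 41% |
| AR(1) 0.5 | 56% | 33% |
| AR(1) 0.7 | 69% | 47% |
| AR(1) 0.9 | 98% | 88% |

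Now let the full 0.87 be present at visits 3, 5 and 7. On changes, every between-visit contrast of the arm difference is 0.87 − 0.87 = 0, so the interaction can reject only at its significance level, about 5%. For the same effect (CS 0.5, AR(1) 0.5 and 0.7), the arm main effect on changes has 85 to 95% power, and the interaction with visit 1 in the vector has 74 to 88%.

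**Type I error of time-by-arm at nominal 5%** (20,000 null trials per scenario, Monte Carlo SE about 0.15 points):

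| Covariance | Epsilon, 4 occasions | Uncorrected, 4 occasions | Greenhouse-Geisser, 4 occasions | Uncorrected, changes |
|---|---|---|---|---|
| CS 0.5 | 1.00 | 5.2% | 5.0% | 5.2% |
| AR(1) 0.5 | 0.86 | 6.0% | 5.1% | 5.3% |
| AR(1) 0.7 | 0.77 | 6.2% | 4.9% | 5.4% |
| AR(1) 0.9 | 0.68 | 7.0% | 5.1% | 5.6% |

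With SD rising from baseline, the uncorrected rates are 5.2 to 6.8% (four occasions) and 4.8 to 6.1% (changes).

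**The case against.** A reader might infer that the plan places visit 1 in the response and takes uncorrected P values, so that its tests are invalid and its arm effect diluted. The document says neither. The grammar leans towards changes, and on that reading no baseline term dilutes the effect. The article is silent on sphericity, and the choice of correction is commonly left to a fuller document that is not shown. With Greenhouse-Geisser or the multivariate test, the simulated error rates are 4.7 to 5.2%. Silence on the correction is therefore no finding in itself, and the inflation is conditional and small.

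A reader might also set the weak arm main effect against the stronger visit-7 comparison and conclude that the trial loses power for its main question. It does not. The visit-7 change is the primary outcome with its own test, and an average over visits is a different quantity. With visit 1 in the vector, the interaction, which is the term nearest to the Discussion's stated purpose, is not diluted.

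Nor can the 40-mm entry rule be used to argue that baseline is truncated. Pain is rated at screening, baseline is visit 1, the document does not say the two scores are the same, and ODI has no entry threshold.

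All of this stands, and it limits the point. It does not rescue the method as named: under either reading one of the two terms can mislead, and both layouts forgo the precision of a baseline covariate.

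**Conclusion.** The point holds as a free improvement to two secondary analyses. It is not an error in the trial's main inference.

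- **Visit 1 as a response occasion:** a linear effect on the arm main term is multiplied by 0.75, with power about 36 to 62%.
- **Changes as the response:** the time-by-arm term has no power beyond its significance level against an early, sustained effect.
- **Baseline-adjusted average over visits 3, 5 and 7:** about 77 to 98% power for the linear effect, above the arm effect in either layout under each equal-SD covariance assumed.
- **Sphericity:** a side issue. It adds one to two percentage points of type I error at most, and only if the F test is uncorrected and the correlation is serial.

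The factor 0.75 follows from a linear effect. The zero interaction follows from a constant one. The power and error rates rest on assumed covariances, complete data and 52 patients per arm.

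**What to change.** In the Statistical analysis section, replace RM-ANOVA for the all-visit VAS and ODI outcomes with a mixed model for repeated measures. The response is the score at visits 3, 5 and 7. The terms are arm, visit, arm-by-visit, baseline value and baseline-by-visit, with unstructured covariance. Fit it to all observed data without LOCF. Report the arm difference with its 95% CI at each visit. Do not let the arm-by-visit P value stand alone as the test of efficacy, because with three post-baseline visits it is as blind to a constant effect as the interaction on changes.

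If RM-ANOVA is kept, use baseline as a covariate and not as a response occasion, apply the Greenhouse-Geisser correction, and name the tested term. Align the Discussion's sentence on RM-ANOVA with whichever is chosen.

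The cost is wording only. The SPSS MIXED procedure covers the model, and no new data, visits or patients are needed. The wording should be settled before unblinding.

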## Discussion

3

Of late, nonpharmacological therapies for chronic low back pain have gained popularity as replacements for medication or surgery. In the field of oriental medicine, various treatments, such as acupuncture, electroacupuncture, pharmacopuncture, and acupotomy, are used for chronic low back pain.

Magnetic fields are used to treat various diseases.^[18]^ Use of electromagnetic stimulation therapy has been reported for inducing muscle relaxation,^[9]^ treating Bell palsy^[19]^ as well as musculoskeletal pain.^[20,21]^ To the best of our knowledge, this will be the first study on the use of electromagnetic acupuncture for the treatment of chronic low back pain.

This study design is expected to have some advantages. In order to verify the efficacy of electromagnetic acupuncture for chronic low back pain, the acupoints and procedure have been standardized. In addition, the placebo device will appear and sound, and be used, in the same way as the Whata153, ensuring a double-blind protocol. Moreover, RM-ANOVA will be used to assess not only the reduction in pain at a certain point in time but also differences in the amount of pain reduction over time.

The results of this trial will provide important clinical information about the efficacy and safety of electromagnetic acupuncture, which is expected to cause less discomfort and provide better results than electroacupuncture, for chronic low back pain. We believe that this treatment will relieve pain and improve the quality of life for many patients experiencing chronic low back pain. Because this is a pilot trial, we will analyze the data from various aspects and use statistical methods that will help in providing a foundation for the final clinical trial. If this study is successful, we expect that further studies on electromagnetic acupuncture for other clinical diseases will be designed and performed.
